### Sample size

To estimate required sample size for adequate power of the clinical trial, we used as primary outcome peripartum depression (PDS) at post-treatment. A study that compared scores on the Edinburgh Postnatal Depression Scale (EPDS) in 132 women divided into two groups, cognitive-behavioral therapy for insomnia (*N* = 89) or control group (*N* = 43), before, during and after pregnancy [35] was used. The software G-Power was used to estimate sample size: 114 women in total would be needed to have an effect power of at least 80%. Drop-out rates in previous studies were around 5 to 16% for post-treatment and short follow-ups [28, 33] and around 17% for 6 months follow-up [36]. We plan to recruit 150 participants, accounting for a dropout rate of 24%.

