**Methods:**

The present protocol outlines a randomized controlled trial aimed at testing the long-term effectiveness of an automatized digitalized psychoeducational intervention for insomnia for expectant mothers complaining insomnia symptoms without comorbidity. Outcomes include physiological, hormonal, and subjective indices of maternal psychopathology, stress, and emotional processes, and sleep and wellbeing of the family system.

The trial is part of a longitudinal study evaluating expectant mothers from early pregnancy (within the 15th gestational week) to 6-months postpartum through 6 observational phases: baseline (BSL), 6- and 12-weeks from BSL (FU1-FU2), 2-to-4 weeks after delivery (FU3), and 3- and 6-months after delivery (FU4-5). We plan to recruit 38 women without sleep difficulties (Group A) and 76 women with sleep difficulties (Group B). Group B will be randomly assigned to digital psychological control intervention (B1) or experimental psychoeducational intervention targeting insomnia (B2). At 3 time points, an ecological-momentary-assessment (EMA) design will be used to collect data on sleep and emotions (diaries), sleep-wake parameters (actigraphy) and stress reactivity (salivary cortisol). We will also test the DNA methylation of genes involved in the stress response as biomarkers of prenatal poor sleep. Information on partner’s insomnia symptoms and new-borns’ sleep will be collected at each stage.

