### Screening

Following our recruitment strategy, all women at the first ultrasound check or all women expressing interest through the study’s website will be contacted for an appointment with a clinical psychologist for the screening, which will be conducted in a confidential space in a room at the Universities’ Department involved (Department of Biomedical and Neuromotor Sciences, University of Bologna; Department of Human Sciences, Guglielmo Marconi University of Rome). This space will be used for all in-person contact with the participants (detailed below). Study’s materials, including biological samples, will all be conserved labelled with pseudonymized codes (number and letters without personal information) in a secured room in the Department of Biomedical and Neuromotor Sciences, University of Bologna for the duration of the study. A member of the research team will explain study aims and procedure. All women will be asked to read and sign the informed consent before proceeding. A separate informed consent will be asked for the use of salivary samples for the analyses of cortisol level and DNA-methylation (see “Baseline” section). Screening will be evaluated through a psychological structured interview (Structured Clinical Interview for DSM-5, SCID-5 in the brief version QuickSCID-5) [37] and a specific interview about their sleep [38] by clinical psychologists ([name], [name], [name]). Information on pregnancy and socioeconomic variables will be collected. Women will be asked to share along with their consent, gynaecological medical data on their health status (e.g. information on pregnancy).

Eligible participants will be divided in two groups:*Group A*: control group of healthy pregnant women with no insomnia complaints (*N* = 38);*Group B*: pregnant women complaining of subthreshold or clinical insomnia (*N* = 76).

Insomnia categories (absence of insomnia; subthreshold insomnia; clinical insomnia) will be operationalized using the validated questionnaire ‘Insomnia Severity Index’ (ISI) [39]. ISI is a measure of insomnia severity in the 2 weeks before compilation. Participants provide answers on a five-point Likert scale on 7 items. The score is the simple sum of the answers to all the questions and can range from 0 to 28. The total score is interpreted as follows: no insomnia (0–7); subthreshold insomnia [8–14]; clinical insomnia [15–28].

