### Randomization

Participants in Group B will be randomly assigned to one of the following two subgroups:

*Subgroup B1* (active control): psychological placebo (*N* = 38);

*Subgroup B2* (intervention): psychoeducation based on CBT-I adapted to pregnancy (*N* = 38).

Allocation concealment will be performed in steps: firstly, a code has to be created for each future participants to set the online platform they will use. The alphanumeric code (here referred to as “ID-code”) is composed of a string of numbers and the subgroup (B1 or B2). The ID-codes will be created before the start of the study by a computerized generator of random numbers. Each participant, upon allocation, will receive a folder with their ID-code, together with the instruments and information for the baseline phase (see below). A member of the research team who will not conduct screening and assignment to groups will prepare the sealed folders containing the ID-codes. The folders of Group B will be shuffled and then sequentially numbered. After the screening, each participant entering the study in the Group B will be given a numbered folder labelled with the letter “B”. With this procedure, participants will be randomly assigned to subgroup B1 or B2, concealing allocation to both participants and the investigator. Neither the psychologists conducting the screening interviews, nor the participants will know the allocation until after the screening.

Participants in the passive control condition (*Group A*) will also receive a randomly generated ID-code.

Participants will be given the credentials to log-in to their personal area on the website of the study for the next phases. The credentials will match the ID-code and thus each condition will have access to the respective online contents. The ID-codes will be used for each subsequent phase of the study.

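### The 114 women behind the power claim include 38 who are never randomised, and the 38/76 recruitment figures conflict with the target of 150

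*Protocol article*

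**What the plan says.** The Sample size section names the sizing endpoint: "we used as primary outcome peripartum depression (PDS) at post-treatment", measured by the EPDS. The evidence behind it is a study "in 132 women divided into two groups, cognitive-behavioral therapy for insomnia" or control (89 and 43 women). It adds that "The software G-Power was used to estimate sample size", and that "114 women in total would be needed to have an effect power of at least 80" per cent. No effect size, mean difference, SD, sidedness or test family is given.

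The same section continues: "We plan to recruit 150 participants, accounting for a dropout rate of 24" per cent. The Participants section repeats 150 as the number at which recruitment stops.

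The group sizes appear in three other places:

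- Abstract, Methods: "We plan to recruit 38 women without sleep difficulties (Group A) and 76 women with sleep difficulties (Group B"), a total of 114.
- Screening: Group A, a "control group of healthy pregnant women with no insomnia complaints", has N = 38, and Group B has N = 76.
- Randomization: only Group B is randomised, to B1 (psychological placebo, N = 38) or B2 ("psychoeducation based on CBT-I adapted to pregnancy", N = 38).

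The primary hypotheses compare intervention with control at post-treatment. The Expected results section makes clear that the comparator is the placebo group.

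**The concern.** The two problems are linked.

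First, the power figure is not tied to the comparison that it should support. A total derived from a two-group treatment study would normally be the total for the two randomised arms. Here one third of it is a healthy comparison group selected by a low ISI score, which adds nothing to a direct B1-versus-B2 test of EPDS.

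Second, 114 serves both as the number to recruit (abstract) and as the number left after dropout from 150 (Sample size). Whoever prepares the numbered Group B folders in advance cannot tell from the article how many are needed.

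At stake is how a null EPDS result is read. Reported against a claim of at least 80% power, it would look like evidence of no effect, although the randomised arms may not have had that power.

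**Working it through.** **1. The plan's own figures.** The dropout step reproduces: 114 / (1 − 0.24) = 150, and 150 × 0.76 = 114. The split is 38 + 38 + 38 = 114, so the randomised contrast has 114 − 38 = 76 women. The 114 itself cannot be reproduced, because the effect size and test are not given.

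**2. Method.** For each plausible origin of 114, I solved for the standardised difference d that gives 80% power and then applied it to B1 versus B2. Alpha is 0.05 (Statistical analysis section); two-sided testing is my assumption. For a two-sample t-test the noncentrality is d × √(n1·n2/(n1+n2)) on n1+n2−2 degrees of freedom, and power is the probability that the noncentral t exceeds the critical value in absolute size.

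**3. If 114 was a two-group total.**

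| Assumed origin of 114 | d for 80% power | Two-sided power, 38 v 38 |
|---|---|---|
| 57:57, two-sided | 0.529 | 62.5% |
| 76:38, two-sided | 0.561 | 67.6% |
| 77:37 (the cited study's 89:43 ratio), two-sided | 0.565 | 68.2% |
| 76:38, planned one-sided | 0.497 | 57.1% |

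This gives about 57 to 68% across the readings shown. They are illustrations, not bounds; a one-sided 57:57 plan would fall lower.

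**4. If 38 per arm was the two-group result and an equal Group A was added.** Then d = 0.651, and power is 80.0% with 38 analysed per arm. If only 38 per arm are randomised, dropout reduces it:

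| Dropout | Analysed per arm | Power |
|---|---|---|
| 5% | 38 × 0.95 ≈ 36 | 77.8% |
| 16% | 38 × 0.84 ≈ 32 | 72.7% |
| 24% | 38 × 0.76 ≈ 29 | 68.3% |

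The 5 to 16% is the article's own range for post-treatment and short follow-ups; 24% is its overall allowance.

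**5. If 114 came from a three-group one-way ANOVA.** With N = 114 and 80% omnibus power, f = 0.295. The B1-versus-B2 difference then depends on the pattern of the three means:

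- B1 and B2 are the extremes, with A midway: d = f√6 = 0.722, power 87.4% at 38 per arm.
- B1 or B2 differs from the other two groups, which are equal: d = 3f/√2 = 0.625, power 76.7%.
- Equally spaced means, with B1 and B2 adjacent: d = f√6/2 = 0.361, power 34.2%.

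**6. Splitting the 150.** Allocating 50/50/50 leaves 50 × 0.76 = 38 per group. That meets the 38/38/38 target, and it restores 80% power only if the planning effect was about 0.65 or larger.

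**The case against.** The strongest reply is that nothing stated is arithmetically wrong and no power failure is shown. Since 114 is exactly 3 × 38, it fits a two-group calculation of 38 per arm with a third group of equal size added, and then 38 completers per arm deliver 80%. A three-group calculation is also plausible, because the design section describes three parallel arms and the mixed model uses all three groups; one pattern of means gives 87%. The planned longitudinal model could also gain precision over a simple post-treatment t-test: under the 57:57 reading, adjusting for baseline with an assumed correlation of 0.5 raises power from 62.5% to about 75%.

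These points stand. A reader might infer that the randomised comparison is certainly underpowered; the article does not support this, because it does not state the effect size or test.

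A reader might also infer that dropout was ignored. That is not so either: 150 with 24% dropout is an allowance, and outside the abstract the 38s can be read as analysable targets. Nor is 29 per arm the natural count for the sizing endpoint, given the 5 to 16% dropout cited for post-treatment.

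What the reply does not remove is the conflict. The abstract gives 114 as the number to recruit, two other sections give 150, the 150 is never divided among the groups, and the power sentence does not say which comparison it describes.

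**Conclusion.** The point holds as an inconsistency in figures on which the trial relies, with a conditional loss of power.

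Certain from the text: the 114 includes 38 women who are never randomised, the treatment contrast has 76, and the recruitment figures of 114 and 150 disagree. A separate analysis plan could not make the two recruitment figures agree.

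Conditional on how 114 was derived is the size of any shortfall, for which only the ranges in the working can be given. They assume a two-sided 5% t-test at post-treatment without covariate adjustment. The two-group source study and the reference to a total favour the less comfortable two-group reading, but do not establish it.

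**What to change.** In Sample size, state the power for the randomised B1-versus-B2 contrast on EPDS at follow-up 1, with the assumed mean difference, SD, test and sidedness. For example: 38 analysed women per arm give 80% power, two-sided 5%, for a standardised difference of about 0.65. If the planning effect was smaller, restate the power downward.

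Label 38/38/38 as the analysable targets. Give the recruitment split of the existing 150 in the same terms in the abstract, Participants, Sample size, Screening and Randomization sections. One split that works is 50 in Group A, 50 in B1 and 50 in B2, which means 100 Group B folders.

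The cost is wording and a matching registry update; the 150 need not change. Splitting the 150 does not by itself cure a shortfall if 114 was meant as the analysable total for the two randomised arms. In that case 57 / 0.76 = 75 per arm would have to be randomised, 150 in Group B alone with Group A on top, or the lower power accepted and stated.

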### Screening

Following our recruitment strategy, all women at the first ultrasound check or all women expressing interest through the study’s website will be contacted for an appointment with a clinical psychologist for the screening, which will be conducted in a confidential space in a room at the Universities’ Department involved (Department of Biomedical and Neuromotor Sciences, University of Bologna; Department of Human Sciences, Guglielmo Marconi University of Rome). This space will be used for all in-person contact with the participants (detailed below). Study’s materials, including biological samples, will all be conserved labelled with pseudonymized codes (number and letters without personal information) in a secured room in the Department of Biomedical and Neuromotor Sciences, University of Bologna for the duration of the study. A member of the research team will explain study aims and procedure. All women will be asked to read and sign the informed consent before proceeding. A separate informed consent will be asked for the use of salivary samples for the analyses of cortisol level and DNA-methylation (see “Baseline” section). Screening will be evaluated through a psychological structured interview (Structured Clinical Interview for DSM-5, SCID-5 in the brief version QuickSCID-5) [37] and a specific interview about their sleep [38] by clinical psychologists ([name], [name], [name]). Information on pregnancy and socioeconomic variables will be collected. Women will be asked to share along with their consent, gynaecological medical data on their health status (e.g. information on pregnancy).

Eligible participants will be divided in two groups:*Group A*: control group of healthy pregnant women with no insomnia complaints (*N* = 38);*Group B*: pregnant women complaining of subthreshold or clinical insomnia (*N* = 76).

Insomnia categories (absence of insomnia; subthreshold insomnia; clinical insomnia) will be operationalized using the validated questionnaire ‘Insomnia Severity Index’ (ISI) [39]. ISI is a measure of insomnia severity in the 2 weeks before compilation. Participants provide answers on a five-point Likert scale on 7 items. The score is the simple sum of the answers to all the questions and can range from 0 to 28. The total score is interpreted as follows: no insomnia (0–7); subthreshold insomnia [8–14]; clinical insomnia [15–28].

Group A (passive control group) will serve as a comparator for the absence of any intervention, accounting for natural changes in sleep during pregnancy.

### Randomization

Participants in Group B will be randomly assigned to one of the following two subgroups:

*Subgroup B1* (active control): psychological placebo (*N* = 38);

*Subgroup B2* (intervention): psychoeducation based on CBT-I adapted to pregnancy (*N* = 38).

Allocation concealment will be performed in steps: firstly, a code has to be created for each future participants to set the online platform they will use. The alphanumeric code (here referred to as “ID-code”) is composed of a string of numbers and the subgroup (B1 or B2). The ID-codes will be created before the start of the study by a computerized generator of random numbers. Each participant, upon allocation, will receive a folder with their ID-code, together with the instruments and information for the baseline phase (see below). A member of the research team who will not conduct screening and assignment to groups will prepare the sealed folders containing the ID-codes. The folders of Group B will be shuffled and then sequentially numbered. After the screening, each participant entering the study in the Group B will be given a numbered folder labelled with the letter “B”. With this procedure, participants will be randomly assigned to subgroup B1 or B2, concealing allocation to both participants and the investigator. Neither the psychologists conducting the screening interviews, nor the participants will know the allocation until after the screening.

Participants in the passive control condition (*Group A*) will also receive a randomly generated ID-code.

Participants will be given the credentials to log-in to their personal area on the website of the study for the next phases. The credentials will match the ID-code and thus each condition will have access to the respective online contents. The ID-codes will be used for each subsequent phase of the study.

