### Blinding

The screening procedure, including the clinical interviews, will be conducted before group allocation. Members of the research team scoring actigraphic data and analysing salivary samples will be blinded to participants’ allocation. Statistical analysis will be conducted on participants’ data associated with the random number labelled with the ID-code without the letter identifying the group allocation.

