### Baseline

All participants will be asked to log-in to the study website using their personal credentials and to fill in a set of questionnaires (described in “Instruments”). Participants’ sleep and emotional processes will be monitored for 7-days through an ecological-momentary-assessment (EMA) design, which allows repeated experience sampling [40]. The EMA week will include: sleep and emotions diaries (in the morning and evening) to be completed on the website; an actigraphic (wearable wrist device) monitoring sleep-wake variables for 7 days. Under express and separate consents, on the first day of the EMA week, women will be trained to collect, at their home, saliva sample through the saliva swabs they received in their folder. Collection will be carried on in 2 time-points during the day: immediately after awakening and just before bedtime. The saliva sample will be used for evaluation of cortisol levels and for the analysis of DNA methylation of genes involved in the stress response: the FKBP5, the BDNF, and the NR3C1 [41]. Rationales for these analyses are described in “Outcomes”.

Participants will store their samples at home. At the end of the EMA week, participants will be given appointment with the researchers to bring the actigraphy and the saliva samples, closed in an envelope and already marked with unique ID-code.

Participants will be explained that their partners could also take part to the study under their expressed informed consent. Women will be given an informative form directed to partners. Within 3 days from the screening, participants will be contacted via e-mail to assess if their partners are interested to participate. In case of interest, partners’ contacts will be asked. Interested partners will receive an e-mail with their unique credentials to log-in to the website and express their informed consent. In their personal area of the website they will be asked to complete, at each phase of the study, a set of questionnaires: socio-demographic variables for Baseline; the ISI for Baseline and Follow-ups 1–5, a 7-day sleep diary for Baseline and Follow-ups 1 and 5; the Parenting Stress Index (PSI) [42] at Follow-ups 3–5. Participants and partners will be matched through an ID-code and will access their respective unique personal area on the website.

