### Intervention

*Group A* (ISI score under 8) will be observed longitudinally through standard of care above-described procedure, without an active intervention. *Group B* (ISI score above 7) will be randomly assigned to 2 active interventions both conducted through digital therapy: (1) psychoeducation based on CBT-I adapted for pregnancy (experimental intervention; subgroup B2); (2) information on sleep disorders and on peripartum-related issues (placebo intervention; subgroup B1).

Each intervention will share the following characteristics:

fully digitalized on the study website;composed of 6 weekly 20-minutes online sessions;each session will include a before and after brief survey to monitor satisfaction;each participant will start the intervention upon completion of the baseline assessment;participants will be asked to fill out directly on the website a reduced version of the sleep and emotion diaries each day during the intervention (6 weeks).

For Group B1 (placebo), each session will include: educational videos (ca. 20 min) on aspects related to pregnancy and sleep; brief feedback questions. Participants in the placebo intervention will not be given specific indications on skills or techniques for sleep difficulties and will not have access to the weekly chat with the clinician.

Sessions will cover the following contents:

Session 1: phases of pregnancy;Session 2: sleep disorders;Session 3: nutrition and physical activity during pregnancy;Session 4: childbirth;Session 5: psychophysical development of the child in the first year of life;Session 6: synthesis of previous sessions.

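### The ID-code contains the arm (B1 or B2) and is issued before baseline, which contradicts the stated blinding of actigraphy scorers and saliva analysts and puts the baseline phase after allocation

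*Protocol article*

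**What the plan says.** Under Randomization, the ID-code "is composed of a string of numbers and the subgroup (B1 or B2". The codes are generated before the study starts and placed in sealed folders by a team member who does not screen or assign. The section continues: "Each participant, upon allocation, will receive a folder with their ID-code, together with the instruments and information for the baseline phase". Concealment is promised for a limited time: neither the screening psychologists nor the women "will know the allocation until after the screening". For website access, "The credentials will match the ID-code", and the code stays in use in all later phases.

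Under Baseline, women log in with these credentials to complete the questionnaires. At the end of the seven-day monitoring week they bring back the actigraph and saliva samples, "closed in an envelope and already marked with unique ID-code". Follow-up-1 and Follow-up-5 repeat this procedure. Under Ethical aspects, the database carries the same codes.

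Under Blinding, "Members of the research team scoring actigraphic data and analysing salivary samples will be blinded to" allocation. The section adds that the statistical analysis will use the code without its group-identifying letter. Under Intervention, "each participant will start the intervention upon completion of the baseline assessment".

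**The concern.** Two things do not fit together.

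First, anyone who sees the ID-code sees the subgroup, and the article puts that code on the material and data that the blinded assessors work from. Of the eight primary outcomes, six are self-reported by women who will experience their own module. Only actigraphic sleep efficiency and salivary cortisol come from another source, so they are the trial's main safeguard against expectation effects. That safeguard depends on the assessors not knowing the arm.

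Second, the code is opened before any baseline-phase measurement. Baseline values serve best as pre-randomisation measurements. Here they are taken after the woman holds a code that names her subgroup, and a woman who leaves during the baseline week has already been randomised. Since the module starts only after baseline, nothing in the design requires this order.

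**Working it through.** No arithmetic applies beyond counting outcomes. The check follows the ID-code through the article.

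**Order of events**

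1. Screening: interviews, pregnancy and socioeconomic information, and the ISI that classifies women into Group A or B (Screening). The Blinding section places this before allocation.
2. Allocation: the Group B woman receives a sealed folder, labelled outside with the letter B and a number. It contains the arm-bearing code and the baseline instruments (Randomization).
3. Baseline phase: questionnaires by log-in, diaries, seven days of actigraphy, saliva on the first day (Baseline).
4. Return of actigraph and saliva under the ID-code, at an appointment (Baseline).
5. Start of the module (Intervention).
6. Follow-up-1 and Follow-up-5: the same monitoring week with the same code.

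Step 2 comes before step 3, so every baseline-phase measure follows allocation. Step 1 comes before step 2, so the screening ISI and interview data do not.

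**Where the code appears, against the blinding stated**

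| Place | Label described | Does it show B1 or B2? |
|---|---|---|
| Website log-in | Matches the ID-code | Yes |
| Returned actigraph and saliva | ID-code | Yes |
| Stored material (Screening) | Pseudonymised code of numbers and letters | Not stated; no separate laboratory code is described |
| Database (Ethical aspects) | ID-code | Yes |
| Statistical analysis (Blinding) | ID-code without the letter | Yes, if only the letter is removed |

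The actigraphy scorers are two trained investigators (Wrist actigraphy), and the study investigators have access to the database (Ethical aspects). No step is described that removes the subgroup before scoring or assay.

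**The stripping step.** The subgroups are B1 and B2. Both contain the letter B and differ only in the digit. Removing the letter leaves a 1 or a 2, which still separates the arms. The sentence masks the arms only if it means the whole suffix.

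**Outcomes exposed through the assessors.** Primary outcomes: 8. Self-reported: EPDS, ISI, GAD-7, affective valence, affective arousal, CERQ subscales, which makes 6. The remaining 8 − 6 = 2 are sleep efficiency and cortisol. Sleep efficiency rests on human scoring by consensus, where knowledge of the arm can enter. Cortisol is read by LC-MS/MS, where it can hardly enter.

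**The case against.** The strongest reply is that the article states that assessors are blinded and never says which label they see on a tube or an actigraphy file. Relabelling before assay or scoring is a detail that a condensed article may leave out. This stands in part: a reader might infer that the blinding has failed in practice, and the article does not show that. What it shows is a labelling scheme incompatible with the blinding it claims, so the text needs repair even if practice is sound.

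Four further readings are tempting and not supported:

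- **That all eight primary outcomes are compromised.** The article claims no participant blinding after allocation. Once the module starts, women see its content, so the code adds little to follow-up self-reports. Cortisol is little exposed.
- **That a woman lost in the baseline week has no baseline data.** She still has the screening ISI, interview results and background information, all collected before allocation.
- **That early loss or arm knowledge must bias the comparison.** Women are not said to be told what B1 and B2 mean, both modules are presented as active, and neither opens before baseline is complete. Bias would need loss or reporting that differs by arm before any arm content is received.
- **That the analyst cannot fit a Group factor once the code is stripped.** Masked group labels are compatible with the article and may be described in an analysis plan that is not shown.

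Allocation concealment up to the end of screening is not in question: sealed, shuffled folders prepared by someone outside screening are adequate for that purpose.

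**Conclusion.** The point holds as an internal contradiction with a cheap remedy. The arm is written into the code used throughout the trial, and the article describes nothing that hides it from the actigraphy scorers or saliva analysts. The one masking step described serves only the statistical analysis and, read literally, does not mask B1 against B2.

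Its reach is two of eight primary outcomes through the assessors, with a credible route to bias for one of them, actigraphic sleep efficiency. Separately, the whole baseline phase follows allocation for the 76 women planned for Group B, apart from what was collected at screening. The amount of bias cannot be derived from the article, and bias in baseline self-reports or from loss in the baseline week is a possibility only.

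The conclusion assumes that the codes are used as written and that no undescribed recoding takes place before scoring or assay. If recoding does take place, the assessor part becomes a correction of wording; the order of allocation and baseline remains.

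**What to change.** - **Code.** Use a participant code made of random digits only, with no subgroup in it. Keep the table linking code to arm with the folder preparer or the website administrator, provided that person does no assessment.
- **Timing.** Run the baseline phase under the neutral code. Release the allocation and unlock the module only after the baseline monitoring week, at the appointment already planned for returning the actigraph and saliva.
- **Blinding text.** State that samples and actigraphy files reach the assessors under the neutral code. Replace the removal of the letter with masked group labels for the statistician.
- **Women already enrolled.** Recruitment was to start in May 2024, so some may hold arm-bearing codes. Relabel their samples and actigraphy files with neutral codes before assay and scoring. This protects assessor blinding for material not yet processed; it cannot change the order of allocation and baseline for these women.

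The cost is regenerating codes, relinking log-ins and partner matching for anyone already enrolled, one linking table, and allocation about a week later. No extra visit is needed.
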